## Abstract

**Background:**

The objective is to present the design of randomised clinical trial (RCT) on the effectiveness of physical therapy added to general practitioners management compared to general practitioners management only in patients with an acute lumbosacral radicular syndrome (also called sciatica).

**Methods/Design:**

Patients in general practice diagnosed with an acute (less than 6 weeks) lumbosacral radicular syndrome and an age above 18 years are eligible for participation. The general practitioners treatment follows their clinical guideline. The physical therapy treatment will consist of patient education and exercise therapy. The primary outcome measure is patients reported global perceived effect. Secondary outcome measures are severity of complaints, functional status, health status, fear of movement, medical consumption, sickness absence, costs and treatment preference. The follow-up is 52 weeks.

**Discussion:**

Treatment by general practitioners and physical therapists in this study will be transparent and not a complete "black box". The results of this trial will contribute to the decision of the general practitioner regarding referral to physical therapy in patients with an acute lumbosacral radicular syndrome.

## Background

### Why a design article?

Publishing the design of the trial has several advantages. It may prevent publication bias [1]. A study producing positive results seems more likely to be published than a study that reports no or negative results [2,3]. Also, the study can be included in systematic reviews because data can be retrieved from the researcher [2]. Publishing the design of a study before the results are available provides an opportunity to reflect critically on the design of the study, irrespective of the results. Also, a design article provides detailed information about the intervention within the trial to care givers.

The lumbosacral radicular syndrome (LRS) is a complex of symptoms related to the lumbosacral nerve roots. The LRS is a disorder with radiating pain in the leg below the knee in one or more lumbar or sacral dermatomes, and can be accompanied by phenomena associated with nerve root tension or neurological deficits (i.e. sensory deficits in the leg, decreased muscle strength in the leg, decreased reflexes, urinary problems) [4-7]. A prolapsed disc is a frequent cause of LRS, but other causes include spinal or lateral recess stenosis, tumours and radiculitis [4,5,7,8]. The incidence of LRS in the Netherlands is estimated at 5 per 1000 persons a year [8].

Most patients seeking medical care in the Netherlands will first visit a general practitioner (GP), who is regarded as the 'gatekeeper' of the health care system. The majority of health problems presented to GPs are treated by the GPs themselves and they are responsible for most referrals to (para) medical specialists. In 1996 the Dutch College of General Practitioners published their clinical guideline for LRS [5]. There is consensus that treatment of LRS in the first six to eight weeks should be conservative. The exact content of the conservative treatment is yet not clear [9]. Since the study of Vroomen et al. [10] bed rest is not regarded a treatment option for LRS anymore.

Primarily, treatment consists of adequate pain medication, giving information about the natural course of LRS, which in general is favourable, and stimulating to continue the normal daily activities of the patient. GPs in the Netherlands largely comply with the recommendations stated in the clinical guideline regarding management in patients with LRS [11]. However, they deviated regarding the referral to physical therapy (PT), almost half of patients with LRS were referred, whereas this was not recommended in the guideline. No specific patients characteristics could be found for the prescription of physical therapy. So, in general practice referral to PT in patients with LRS is common. However, there is a lack of knowledge of the effectiveness of PT in LRS. Therefore, the aim of this article is to present the design of a randomised clinical trial of conservative treatment (general practitioners and physical therapy) in patients with acute LRS.

## Methods/Design

### Aim

The LRS trial aims to assess the effectiveness of PTs management added to GPs management compared to GPs management only in patients with acute LRS. We will use a multicentre, randomised clinical trial as study design. Figure 1 shows the flow chart of the proposed design of the LRS trial. The procedures and design of this study are approved by the Erasmus Medical Center Ethics Committee.

### Study population

Participating GPs in and around Rotterdam, the Netherlands, will invite patients with suspected acute LRS to participate in the trial. GPs will invite patients from May 2003 till November 2004 if they have radiating (pain) complaints in the leg below the knee; duration of the (pain)complaints is less than 6 weeks, the age is above 18 years and they present one of the following symptoms: more pain on coughing, sneezing or straining, decreased muscle strength in the leg, sensory deficits in the leg, decreased reflex activity in the leg or a positive straight leg raising test. Patients will receive a letter of information about the LRS trial from their GP. Patients' name and telephone number will be faxed to the research institute. Subsequently, a researcher (PL) will screen eligible patients by telephone and make an appointment to check inclusion and exclusion criteria, to complete the informed consent procedure and to perform the baseline measurement. Figure 2 shows the criteria that must be fulfilled to participate in the LRS trial. A research assistant will check these criteria during patients first visit. The informed consent procedure is completed when patients meet the criteria, are willing to participate and give their written consent. Hereafter, the baseline measurement will take place.

### Randomisation

Randomisation will take place after baseline measurement by the research assistant. We use a concealed randomisation procedure using a computer generated randomisation list developed by an independent person. Patients' specific and unique trial number will be typed in a special developed database (i.e. not editable for research assistant and a second randomisation action using the same trial number is not possible) and the random allocation will appear on screen. In order to prevent unequal treatment group sizes, block randomisation will be used with blocks of 10 patients [12]. This means that after every 10th patient the number of patients allocated to both treatment groups is equal. Towards every randomised patient will be explained that the management of their complaint by his or her GP will be continued. Patients who are allocated to physical therapy will be shown a list of participating physical therapists of which he or she can make a choice. The research assistant makes the first appointment with the physical therapist most easily accessible by the patient.

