### Blinding

For obvious reasons GPs and PTs are not blinded for treatment allocation. But they are not involved with treatment effect measurements. The patients cannot be blinded because of the ethical reasons as stated by the Medical Ethical Committee. The researcher is involved in the statistical analysis, but the analysis and interpretation of the findings will be audited and verified by an independent and not involved statistician. In this trial the primary outcome measurement and most of the secondary outcome measurements will be scored by the patients. Studies from Ostelo et al [13] and Scholten-Peeters et al [14] mentioned that in this type of study patients are blinded to a certain extent because they are unaware of the exact content of both treatments or may be called naive to the content of the treatment not received. Other more or less similar designed trials from Vroomen et al [10] and Hofstee et al [15] reported that it is not possible to blind participating patients for allocated treatment. Therefore, we think it is important to know any treatment preference of the patients at baseline. Supplementary analysis may show to what extent this effects the scores on outcome measurements of the patients.

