### Sample size

This trial attempts to enrol 182 patients with LRS, 91 patients in both treatment groups. This sample size is regarded sufficient to detect a difference of 20% (with a α of 0.05 and a power of 80%) in the primary outcome (GPE) between the two treatment groups. A difference of 20% is considered to be clinically relevant [17].

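### The fixed, stated block length of 10 on one trial-wide list weakens allocation concealment for patients late in a block; as an upper bound, one allocation in six is certain in advance

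*Protocol article*

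**What the plan says.** The protocol article, Randomisation, fixes one block length: "block randomisation will be used with blocks of 10 patients". It spells out the consequence: "This means that after every 10th patient the number of patients allocated to both treatment groups is equal". No strata are named, so the text describes one sequence for the whole multicentre trial.

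On who does what:

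- Randomisation: "Randomisation will take place after baseline measurement by the research assistant". The assistant enters the trial number, reads the allocation on screen and books the first physical therapy appointment.
- Study population: "A research assistant will check these criteria during patients first visit". A researcher does the telephone screening and makes that appointment. Consent precedes the baseline measurement; the person who takes it is not named.
- Blinding: "The patients cannot be blinded because of the ethical reasons as stated by the Medical Ethical Committee". Patients score the primary outcome, global perceived effect, themselves.

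The procedure is described as concealed. The safeguards given are a computer-generated list made by an independent person, a database that the assistant cannot edit, and a bar on a second draw for the same trial number.

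**The concern.** Concealment requires that whoever decides on a patient's entry cannot foresee the next allocation. With a constant block length and open treatment, past allocations reveal future ones: once five patients in a block have gone to one arm, the rest of that block must go to the other. The role that sees the past allocations is also the role that checks the next patient's eligibility.

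The stated safeguards prevent altering or repeating an allocation. They do not prevent prediction from a tally. Randomising after consent and baseline does not help either, because the earlier allocations are known before the next patient's first visit.

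At stake is selective inclusion by prognosis or by apparent wish for physical therapy. In an unblinded trial whose primary outcome is the patient's own rating, such selection would shift the comparison directly. The article itself regards treatment preference as important enough to record at baseline.

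**Working it through.** **Inputs**

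- Block length 10, five per arm, one sequence: "after every 10th patient the number of patients allocated to both treatment groups is equal" (Randomisation).
- Total: "This trial attempts to enrol 182 patients with LRS, 91 patients in both treatment groups" (Sample size). This is 18 full blocks (180 patients) plus 2.
- Not stated, so assumed and varied below: the number of assistants, and whether they know the block length and keep a tally.

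**The plan's own figure.** The article gives no predictability figure. Its 182 serves here only as a denominator. It can be reproduced, with an assumed control rate, from the aim to "detect a difference of 20% (with a α of 0.05 and a power of 80%) in the primary outcome (GPE"): for 50% versus 70%, two-sided, n per arm = 7.849 × (0.25 + 0.21) / 0.20² = 90.3, so 91. The control rate is not stated, and nothing below depends on it.

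**Step 1: allocations known with certainty.** There are C(10,5) = 252 equally likely blocks. The allocation at position k + 1 is certain if one arm is already full after k patients, which has probability 2 × C(k,5) / 252 for k from 5 to 9.

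| Position | Calculation | Chance that it is certain |
|---|---|---|
| 1 to 5 | – | 0 |
| 6 | 2 × 1 / 252 | 0.8% |
| 7 | 2 × 6 / 252 | 4.8% |
| 8 | 2 × 21 / 252 | 16.7% |
| 9 | 2 × 56 / 252 | 44.4% |
| 10 | 2 × 126 / 252 | 100% |

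The sum is 420 / 252 = 1.667 per block of 10, or 16.7%. This agrees with the closed form 1 / (5 + 1) and with full enumeration of the 252 blocks.

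**Step 2: applied to the trial.** 18 × 1.667 = 30 patients. The two left over occupy positions 1 and 2 of a block and add none. 30 / 182 = 16.5%.

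**Step 3: best guess.** Always guessing the arm with more places left, and tossing a coin at ties, gives 5 + (2¹⁰ / 252 − 1) / 2 = 5 + (4.063 − 1) / 2 = 6.53 correct of 10. That is 65.3%, against 50% by chance.

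**Step 4: several assistants.** Suppose k assistants share the list equally at random and do not pool what they see. An assistant is certain only if all five patients of the full arm passed through that assistant's hands, so the share is 1/6 × (1/k)⁵.

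- k = 2: 1/6 × 1/32 = 0.52%, or 0.0052 × 182 = about 1 patient.
- k = 3: 1/6 × 1/243 = 0.07%.

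Simulation of 100,000 blocks gave the same figures. If the assistants pool what they see, the 1 in 6 returns.

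**Step 5: effect of varying the length.** A simulated observer saw every allocation and knew the set of possible lengths, but not which was drawn. This observer was certain of about 2.3% of allocations with lengths 4, 6 and 8, and about 1.3% with lengths 8, 10 and 12, compared with 16.5% for fixed blocks of 10.

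**The case against.** The tempting stronger reading is that the claimed concealment is defeated and that one allocation in six is in fact known. The documents do not support it.

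- Even a fully informed observer is uncertain of five allocations in six, and of all of the first five in each block.
- The figure needs one assistant who handles every patient, knows the length and tracks position. The article establishes none of these. Its singular may be generic, and it does not say whether the assistant is told the length or when the article appeared relative to recruitment.
- A reader might infer that the assistant takes consent or controls the timing of visits. The first is not stated, and the appointment is made by a researcher.
- The full entry criteria are in a figure not shown, so the assistant's scope for judgement cannot be assessed.
- Lack of stratification is not the cause. Stratified blocks of a fixed, known length would be just as predictable.
- The plan records treatment preference at baseline and foresees supplementary analysis of it, checks baseline comparability and allows adjustment, so it would be wrong to say that analysis can do nothing.

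All of this stands as a limit on the size of the problem. It does not remove it. The length is fixed and stated, the allocations are visible to the role that checks eligibility, and adjustment reaches only what has been measured.

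**Conclusion.** The concern holds in a limited form. A constant block length of 10 weakens concealment for late-block patients, and the last place in each of the 18 full blocks is always determined. The size runs from under 1% of allocations certain to each assistant (two or more sharing the list without pooling) to 1 in 6, about 30 of 182, as an upper bound (one assistant who sees all allocations, knows the length and keeps a tally). These figures measure predictability. They are not an estimate of bias in global perceived effect, which cannot be derived from the document, and no misuse is suggested. This is a design choice that can be improved cheaply; it is neither an error of calculation nor a contradiction in the article.

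**What to change.** Have the independent person who made the list prepare the remaining sequence with randomly varying block lengths, for example 6, 8, 10 and 12, starting after a completed block. Withhold the lengths and their range from the research assistant and the researcher, and do not publish them until enrolment closes. Because the article already states the present length, only the patients still to be randomised benefit.

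The cost is one new list in the existing database and a possible final imbalance. With a largest block of 12, the arms can differ by at most 6, that is 94 versus 88. Relative precision is then (94 × 88) / (91 × 91) = 8272 / 8281 = 0.999, so the effect on power is negligible. The present scheme does not guarantee 91 per arm either: 182 is not a multiple of 10, and the last two patients may fall in the same arm.

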### Blinding

For obvious reasons GPs and PTs are not blinded for treatment allocation. But they are not involved with treatment effect measurements. The patients cannot be blinded because of the ethical reasons as stated by the Medical Ethical Committee. The researcher is involved in the statistical analysis, but the analysis and interpretation of the findings will be audited and verified by an independent and not involved statistician. In this trial the primary outcome measurement and most of the secondary outcome measurements will be scored by the patients. Studies from Ostelo et al [13] and Scholten-Peeters et al [14] mentioned that in this type of study patients are blinded to a certain extent because they are unaware of the exact content of both treatments or may be called naive to the content of the treatment not received. Other more or less similar designed trials from Vroomen et al [10] and Hofstee et al [15] reported that it is not possible to blind participating patients for allocated treatment. Therefore, we think it is important to know any treatment preference of the patients at baseline. Supplementary analysis may show to what extent this effects the scores on outcome measurements of the patients.

### GP intervention

All patients will be treated by the GP according to their clinical guideline (see Figure 3). GPs will give information and advice about LRS. If necessary they prescribe adequate pain medication. We asked the GPs not to refer patients to paramedical specialists (i.e. manual therapist, physical therapist, exercise therapist, etc.). Referral to PT is based on randomisation and performed by the research assistant.

### PT intervention

PT treatment will imply information and advice about LRS and exercise therapy. Passive modalities such as massage, manipulation techniques or applying applications (e.g. ultra sound or current waves) are not allowed in the PT treatment. This PT treatment protocol was accomplished in a consensus meeting with participating PTs. The PT will report what kind of information/ advice and what type of exercise the patient receives in each session. Both GP and PT intervention will be restricted to a maximum of 9 treatments/ consultations in the first 6 weeks after randomisation.

### Theoretical background

In the Netherlands, PTs are mainly taught the biomechanic model [13]. This model focuses on somatic issues; it assumes a causal relation between tissue damage and pain. PT could be of additional value in the management of patients with LRS because PTs are 'the experts' in treating musculoskeletal disorders with exercises and advice/ information. The pain reported by a patient is used as guidance to determine the intensity of the exercises and the advice about resuming normal daily activities and work. This study assumes that focussing on (pain) complaints with exercises and advice is the optimal PT treatment in the acute phase (0 to 6 weeks) of LRS.

It is possible that patients may suffer from a fear of movement because of pain [16]. Good advice/ information will reassure these patients and exercises will show them that movement is possible. So, the secondary treatment goal of the PT is to decrease the possibly present fear of movement in these patients.

### Sample size

This trial attempts to enrol 182 patients with LRS, 91 patients in both treatment groups. This sample size is regarded sufficient to detect a difference of 20% (with a α of 0.05 and a power of 80%) in the primary outcome (GPE) between the two treatment groups. A difference of 20% is considered to be clinically relevant [17].

### Measurements

Figure 4 shows the outcome measures and the points of time they are collected. At baseline we will collect patients characteristics such as gender, date of birth, height and body weight. In standardised history taking there will be established whether patients are familiar with LRS in the past, report more pain in the leg on coughing/ sneezing or straining, on sitting, standing, walking and lying down, and if patients report a decreased muscle strength and sensory deficits in the leg. The physical examination consists of the straight leg raising test, the crossed straight leg raising test, test of Bragard, finger-floor distance, standing on toes and heels, knee tendon reflex, ankle tendon reflex, strength of m. extensor hallicus longus, sensory tests (touch, sharp and blunt) in the dermatomes L5/ S1 in the feet.

### Primary outcome measure

The primary outcome measure is the Global Perceived Effect (GPE), measured on a 7 points scale ranging from 1 = completely recovered to 7 = vastly worsened. It is regarded a clinical relevant outcome measure and is regarded valid and responsive to measure the patients' perceived benefit [18-20].

### Secondary outcome measures

Pain severity of the leg and the back will be scored on a 11 points Visual Analogue Scale (VAS) ranging from 0 = no pain to 10 = unbearable pain. Reliability, validity and responsiveness of the VAS have been shown [21-23].

The functional status will be measured with the Roland Morris Disability Questionnaire (RDQ) for sciatica [24]. The scoring of the RDQ is achieved by counting the number of positive responses: a patient individual score can vary from 0 (no disability) to 24 (severe disability). The RDQ has proved to be a valid instrument and appears to be responsive for clinical relevant changes [20,25-28].

Health status will be measured by the 36-item short form (SF-36) [29] and the Euroqol (EQ-5D) instrument [30,31]. Validity and responsiveness on both SF-36 [32-34] and EQ-5D [35-37] proved to be sufficient.

Fear of movement will be measured by the Tampa scale for kinesiophobia (TSK) [38,39]. The TSK consists of 17 items; each rated on a 4-point likert scale. The TSK has been shown to be a valid and responsive instrument [40,41].

Costs will be calculated and include LRS related sickness absence from work, medical consumption (i.e. medication use, additional therapies, visits to health care providers), out-of-pocket expenses and paid help. Patients' treatment preference will be evaluated at baseline and at 4 follow-up measurements.

### Statistical analysis

Baseline comparability will be investigated by descriptive statistics to examine whether randomisation was successful. If necessary, adjustments for baseline variables will be performed in the analysis. Group differences and 95% confidence intervals will be calculated for all outcome measures. The statistical analysis will be performed according tot the intention-to-treat principle, analysing the patients in the treatment group to which they were randomly allocated. Between group differences will be calculated using the Student t-test for continuous variables or Chi-Square for dichotomous variables. In addition a per-protocol analysis will be performed, analysing only those patients with no serious protocol deviations. Comparing the results of the intention-to-treat and the per-protocol analysis will indicate if and to what extent protocol deviations might have biased the results. Multivariate regression analysis will be conducted to examine the influence of baseline variables on outcome.

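### Continuous secondary outcomes default to a Student t-test, with baseline adjustment only if judged necessary, so the precision available from each outcome's own baseline score is not secured

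*Protocol article*

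**What the plan says.** The Statistical analysis section of the protocol article names the comparison: "Between group differences will be calculated using the Student t-test for continuous variables or Chi-Square for dichotomous variables". It promises estimates as well as tests: "Group differences and 95% confidence intervals will be calculated for all outcome measures".

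Two other sentences in that section concern baseline data. After a descriptive check of whether randomisation worked, it says: "If necessary, adjustments for baseline variables will be performed in the analysis". Near the end it adds: "Multivariate regression analysis will be conducted to examine the influence of baseline variables on outcome". Neither sentence names a covariate. The first gives no criterion for when adjustment is needed. The second does not say that the regression will supply the treatment effect.

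The outcomes concerned are listed under Secondary outcome measures: leg and back pain (0 to 10), the RDQ ("The functional status will be measured with the Roland Morris Disability Questionnaire (RDQ) for sciatica"), SF-36, EQ-5D and TSK. On timing, the Randomisation section says: "Randomisation will take place after baseline measurement by the research assistant". Follow-up lasts 52 weeks. Four follow-up measurements are mentioned, although only for treatment preference. The schedule for each outcome is in Figure 4, which was not available for this review.

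**The concern.** If these questionnaires are completed before randomisation, each patient brings a measured baseline value of the same scale that will be compared later. A t-test on follow-up scores leaves that information unused, so its interval is wider than it needs to be whenever baseline and follow-up correlate.

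The conditional sentence looks like a remedy but answers a different question. Whether adjustment is worthwhile depends on how strongly baseline predicts outcome. An outcome with perfectly balanced baseline means gains as much precision from adjustment as one with a chance difference. A rule triggered by imbalance can therefore withhold adjustment where it would help.

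An unstated trigger also leaves the choice between adjusted and unadjusted estimates open until data have been seen. The Blinding section says the researcher takes part in the analysis. The audit by an independent statistician is a safeguard, but an auditor can check a model choice only against a rule that was written down.

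What is at stake is the width of the intervals for the secondary outcomes and the firmness of the prespecification. The validity of the trial is not in question.

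**Working it through.** **Inputs.** n = 91 per arm, 182 in total (Sample size section). Two-sided α of 0.05 is assumed, since the article gives 0.05 without sidedness. The correlation r between an outcome's baseline and follow-up scores is not in the article, so it is shown as an assumed range. Data are taken as complete, and results are in units of the outcome's SD.

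**The plan's own figure.** The article gives no precision or power for any secondary outcome. Its only figure is the sample size for a 20% difference in GPE at 80% power, with no control rate stated. At an assumed 50% against 70%, the unpooled two-proportion formula gives

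n = [0.5 × 0.5 + 0.7 × 0.3] × (1.960 + 0.842)² / 0.20² = 0.46 × 7.85 / 0.04 = 90.3, rounded up to 91 per arm.

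So 91 is reproducible under that assumption. It serves below only as the number of patients available.

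**Formulas for the 95% half-width.**
- t-test on follow-up scores: t × √(2/n) = 1.973 × √(2/91) = 1.973 × 0.1482 = 0.293 SD.
- ANCOVA on the outcome's own baseline: t × √(2(1 − r²)/n), so the width is multiplied by √(1 − r²). This ignores the small term for chance baseline difference.
- t-test on change scores (equal SD at both times): the follow-up width multiplied by √(2(1 − r)).

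**Numbers.** At r = 0.3, √(1 − 0.09) = 0.954 and 0.293 × 0.954 = 0.279. At r = 0.5, √(1 − 0.25) = 0.866 and 0.293 × 0.866 = 0.253. Over the range:

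| Assumed r | ANCOVA half-width (SD) | Narrower than follow-up t-test | Change-score t-test half-width (SD) |
|---|---|---|---|
| 0 | 0.293 | 0% | 0.414 |
| 0.1 | 0.291 | 0.5% | 0.392 |
| 0.2 | 0.287 | 2.0% | 0.370 |
| 0.3 | 0.279 | 4.6% | 0.346 |
| 0.4 | 0.268 | 8.3% | 0.320 |
| 0.5 | 0.253 | 13.4% | 0.293 |
| 0.6 | 0.234 | 20.0% | 0.262 |
| 0.7 | 0.209 | 28.6% | 0.227 |

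**Change scores do not remove the point.** The ratio of ANCOVA variance to change-score variance is (1 − r²) / (2(1 − r)) = (1 + r)/2, which is below 1 for every r below 1. A change-score t-test is also 18% wider than the follow-up t-test at r = 0.3, equal to it at r = 0.5, and 22% narrower at r = 0.7.

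**Power, as illustration only.** The t-test has about 80% power at a difference of (1.960 + 0.842) × 0.1482 = 0.415 SD. At that difference ANCOVA has 83.5% at r = 0.3 and 89.8% at r = 0.5. No secondary outcome was powered in the plan, so this shows scale and is not a shortfall against a target.

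**Where imbalance enters.** The observed baseline difference between arms does not appear in the factor √(1 − r²). That is why a rule triggered by imbalance does not track the gain.

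**The case against.** The strongest reply is that the t-test is not wrong. With randomisation and complete data it is unbiased and its interval is valid. The gain depends on a correlation that the article does not give and may be trivial. The same section also allows for baseline adjustment and plans a regression. All of this stands, and it limits the point to efficiency and prespecification. It does not remove it, because the adjustment is conditional on an unstated criterion and the regression is described as a study of baseline influences.

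A second reply is that the full protocol or analysis plan may specify more. That would answer a complaint about silence, but this point concerns a method the article names.

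A reader might go further in four directions that the documents do not support.

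- *The analysis ignores baseline scores altogether.* This is not established. Adjustment is possible under the conditional sentence, and the article does not say whether the t-test uses follow-up or change scores.
- *Patients who miss a visit are dropped, which undermines intention-to-treat.* The article says nothing about missing values, a subject that a condensed article commonly leaves to the full plan. It describes intention-to-treat as "analysing the patients in the treatment group to which they were randomly allocated", which a t-test does not contradict.
- *The comparison is biased by differential dropout.* No retention figure is given, so any size of bias would rest on an invented dropout pattern.
- *The primary analysis or the sample size is affected.* GPE is a rating of perceived change with no baseline score of its own, and the 182 patients were calculated for GPE.

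**Conclusion.** The point holds as a free improvement for the continuous secondary outcomes. The stated default is valid but less efficient than adjustment for the outcome's own baseline, and the conditional rule neither secures that efficiency nor fixes the model in advance.

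Intervals would be 4.6% narrower at r = 0.3, 13.4% at r = 0.5 and 20.0% at r = 0.6, with little to gain below about r = 0.2. These figures assume 91 per arm, complete data, and that the baseline visit collects these scores, which Figure 4 would confirm. The correlation is an assumption, so the direction of the gain is firmer than its size.

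**What to change.** For the continuous secondary outcomes, replace the t-test and the conditional adjustment with a prespecified model. Suggested wording:

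*Each continuous secondary outcome will be analysed by ANCOVA or, where it is measured at several follow-ups, by a longitudinal linear model with arm, visit and arm-by-visit terms. The outcome's own baseline score will be a covariate whatever the observed baseline imbalance. The adjusted difference between arms will be reported with its 95% confidence interval at each visit.*

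The descriptive baseline comparison and the regression on baseline variables can stay, but neither should decide which treatment-effect estimate is reported. The cost is analysis wording and slightly more programming, with no new data. If r proves to be near zero, the covariate costs one degree of freedom and almost no precision.
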